	**Covariates**				
		**Antecedent or confounding variables**			
			Demographic factors	We will gather basic demographic information from all participants including: age, sex, income, educational attainment, marital status, health insurance status, employment type, nativity status and number of years in the United States, and country of origin	
			Anthropometric measurements	Research staff will ascertain measures of height (to the nearest centimeter) and weight (to the nearest 0.1 kg) and will calculate BMI using these values. The waist-to-hip ratio will be derived from abdominal and hip girth obtained using a Gulick II 150- and 250-cm anthropometric tape measure with participants wearing light clothing	
			Acculturation/cultural factors	The Short Acculturation Scale for Hispanics will be used to capture the construct of acculturation in Hispanic/Latino adults [62]. The 10-item scale inquires of language use (Spanish vs English) across settings (home vs social life), language in which entertainment is consumed, and race/ethnicity of individuals across varied social circles. Derived from the Duke University Religion Index [63], religiosity will be assessed using a 5-items scale that includes questions such as, “My religious beliefs are what really lie behind my whole approach to life.” It also assesses frequency of attendance to church services and engagement in religious practices	
			Current health status and medical comorbidities	Self-reported physical and mental health will be measured using the 12-item Short Form Health Survey [64]. Participants will also self-report previous or current existence of any of the following medical conditions: heart attack; congestive heart failure; stroke; diabetes; arthritis; moderate or severe renal disease; fracture of the hip, wrist, arm, or shin; asthma; cirrhosis of the liver or liver disease; cancer; bypass of arteries in the leg; Parkinson’s disease; Alzheimer’s disease or dementia; HIV or AIDS; depression; or anxiety disorder	
			Overall website use	We will also analyze data describing overall use of the website by trial participants, including the number of website logins per participant, average length of screen time per site visit, and extent to which enrollees completed and recorded practicing of at-home exercises	

### Planned Analyses

The primary outcome of the *¡Alégrate!* trial focused on prospective changes in B*P* values, that is, both sitting BP and 24-hour ambulatory readings. The first aim was to examine the efficacy of the intervention in reducing B*P* values immediately postintervention (ie, 5 weeks) and at the 12-week follow-up period, that is, Exams 2 and 3. The second aim was to explore whether the intervention leads to significant improvements in psychological well-being and greater adherence to healthy behavioral practices. We will additionally test whether psychological well-being and healthy behaviors serve as mediators when exploring intervention effects on BP control. The third aim is to test intervention effects on circulating markers of inflammation, specifically high-sensitivity C-reactive protein.

Descriptive statistics, at baseline, will summarize participant characteristics for the full sample and stratified by intervention arm. Bivariate tests will be conducted to compare the intervention and control conditions to ensure compatibility across key variables (eg, demographic factors, well-being profiles, etc) and to test the success of the randomization protocol. Discrepancies in baseline values across conditions will inform covariates for inclusion when testing our main hypotheses of interest. In addition, we will document the number of missing observations over time to assess the potential for bias resulting from significant dropout and differential attrition by condition. We will perform independent sample two-tailed *t* tests and/or Fisher exact tests to compare baseline characteristics of enrollees who completed the trial versus those who prematurely dropped out, allowing us to test possible predictors of attrition.

Given our design and main objective of treatment evaluation, an intent-to-treat analysis will be conducted, where we will consider the data of all participants randomized, with retention of their original intervention assignment. Sensitivity analysis will use multiple imputation procedures across missing values to ensure inclusion of all observations, particularly those resulting from participants who withdraw, are lost to follow-up, or do not complete all assessments. In a supplementary analysis, we will use ordinary or logistic regression (as appropriate, given variable distribution) to implement a dose-response analysis to test whether participation-related factors (eg, number of sessions viewed, rate of homework completion) impact outcomes of interest.

We estimated the sample size requirements of a two-arm randomized trial to evaluate whether our web-based positive psychological intervention resulted in differential and clinically meaningful improvements in systolic BP of 6 mm Hg compared with an attention control condition. A repeated-measures design with systolic BP determination at baseline and 5 and 12 weeks was used. In addition, the following operating characteristics were assumed: (1) a between-subject standard deviation for BP of *σ=12 mm Hg*; (2) a within-subject correlation, *ρ=0.60* (3) a two-sided type I error probability of 0.05; and (4) 80% statistical power. Frison and Pocock [65] argue that adjusting for baseline measures (analysis of covariance) results in a more efficient analysis for a given sample size (larger statistical power). This approach yields an estimate of the required sample size of 28 participants per study arm under equal allocation. Furthermore, assuming a conservative attrition rate of 20%, an updated estimation produces the following sample size of participants per study arm.

[figure not shown]

Stata 15 was used for sample size calculation (*sampsi* command) and all statistical analyses, with effect size estimation derived from published data on the clinical effectiveness of psychotherapeutic interventions to treat hypertension [47,66,67].

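### Covariates are to be chosen from observed baseline imbalance and the 5-week t test ignores baseline BP, although 28 per arm assumes that baseline BP is always adjusted for

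*Protocol article*

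**What the plan says.** Three parts of Planned Analyses in the protocol article bear on this point.

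- **Baseline comparisons.** "Bivariate tests will be conducted to compare the intervention and control conditions to ensure compatibility across key variables". Their stated purposes include "to test the success of the randomization protocol". The next sentence gives the results a further use: "Discrepancies in baseline values across conditions will inform covariates for inclusion when testing our main hypotheses of interest". No significance level or other threshold is given. The list of variables is left open, and BP is not among the examples.
- **Sample size.** The target is "clinically meaningful improvements in systolic BP of 6 mm Hg compared with an attention control condition", with SD 12 mm Hg, within-subject correlation 0.60, "a two-sided type I error probability of 0.05" and "80% statistical power". Systolic BP is measured at baseline, 5 weeks and 12 weeks, and adjustment for baseline by ANCOVA is given as the reason for the efficiency. The result is 28 per arm. With 20% attrition, this matches the total of 70 in the Abstract.
- **Aim 1.** BP at 5 weeks is compared by independent-samples t tests with arm as the grouping variable. Mixed-effects models are also planned for BP at weeks 0, 5 and 12, with time, arm and their product as the listed terms.

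Randomisation is stratified by sex and antihypertensive use (Consent, Assessments, and Randomization). Neither factor is among the listed terms of the Aim 1 models.

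**The concern.** Allocation is computer-generated, blocked, stratified and concealed, so differences between arms at baseline are chance. Testing them says nothing useful about whether randomisation worked. A covariate earns its place by predicting the outcome, whether or not it happens to be unbalanced, so the rule selects on the wrong property. It will also rarely pick sex or antihypertensive use, because stratified blocking balances these by design.

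Two things are at stake. The covariates in the main hypothesis tests would be settled only after the arms had been compared. And baseline BP, the covariate on which the sample size depends, is not guaranteed a place in the 5-week comparison.

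**Working it through.** **Inputs** (Planned Analyses, sample size paragraph): difference 6 mm Hg, SD 12, ρ = 0.60, two-sided α 0.05, power 80%, one baseline and two follow-ups, attrition 20%.

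**Step 1: reproduce 28 per arm.** With no variance reduction:

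n = 2 × 12² × (1.960 + 0.842)² / 6² = 62.79 per arm.

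The Frison-Pocock variance factor for ANCOVA with one baseline and r follow-ups is (1 + (r − 1)ρ)/r − ρ². For r = 2 this is 0.80 − 0.36 = 0.44. Then 62.79 × 0.44 = 27.63, so 28 per arm. Allowing for attrition, 28 / 0.80 = 35 per arm, or 70 in total. The plan's figure is reproduced.

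**Step 2: see which analyses give 28.**

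| Analysis of systolic BP | Variance factor | n per arm | Power at 28 | Power at 35 |
|---|---|---|---|---|
| 5-week value, unadjusted | 1.00 | 63 | 46.4% | 55.2% |
| Mean of two follow-ups, unadjusted | 0.80 | 51 | 55.2% | 64.7% |
| Change to one follow-up | 0.80 | 51 | 55.2% | 64.7% |
| ANCOVA, one follow-up | 0.64 | 41 | 64.7% | 74.4% |
| Change to mean of two follow-ups | 0.60 | 38 | 67.6% | 77.0% |
| ANCOVA, mean of two follow-ups | 0.44 | 28 | 80.5% | 88.4% |

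Of these, only the last gives 28, and it always adjusts for baseline. The powers use the normal approximation.

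**Step 3: simulate the imbalance rule for the 5-week comparison.** There were 40,000 trials per setting, with normal data, SD 12 at both visits, ρ = 0.60 and nothing missing. The rule was read as follows: test baseline systolic BP between arms, use ANCOVA if p is below a cut-off, and otherwise use the t test. The article states no cut-off, so three were tried. Powers are for a 6 mm Hg effect.

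| n per arm | Cut-off (assumed) | Baseline adjusted in | t test only | Imbalance rule | ANCOVA always | Type I error of rule |
|---|---|---|---|---|---|---|
| 28 | 0.05 | 5% | 45.0% | 45.5% | 62.6% | 4.0% |
| 28 | 0.10 | 10% | 45.4% | 46.4% | 62.6% | 3.8% |
| 28 | 0.20 | 20% | 45.2% | 48.0% | 62.3% | 3.2% |
| 35 | 0.05 | 5% | 53.8% | 54.8% | 72.3% | 4.1% |
| 35 | 0.20 | 20% | 54.2% | 57.8% | 72.8% | 3.4% |

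The simulated powers lie slightly below those in step 2 because they use the t distribution.

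**Step 4: find where the loss arises.** At 28 per arm with a 0.05 cut-off, the rule moves power from 45.0% to 45.5%. Always adjusting moves it to 62.6%. The shortfall therefore comes mainly from the unadjusted t test, and the rule does almost nothing to repair it.

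**The case against.** The strongest reply is that baseline BP is not neglected. The mixed model takes BP at week 0 as one of its responses, and the sample size paragraph endorses baseline adjustment. This is right as far as it goes. A reader might infer that baseline BP would enter the analysis in only about 5% of trials, and for the mixed model that is false. Even for the 5-week comparison, 5% requires a 0.05 cut-off and BP among the variables tested, and the article states neither. The mixed model does not close the gap, however. With linear time, equal correlation between visits and a constant 6 mm Hg effect at both follow-ups, its time-by-arm test has 50.3% power at 28 per arm and 59.4% at 35.

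A second reply is that the rule is softer than an automatic test, that Table 2 names candidate covariates in advance, and that data analysis is blinded. This lessens the scope for choosing a favourable model. It does not fix the model, since the choice still depends on baseline differences and the list of variables compared is open. Sex and antihypertensive use are called fixed factors under Overview and Study Design, but the Aim 1 terms do not include them.

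A third reply is that no false-positive harm is shown. This stands. A reader might infer an inflated type I error from a data-dependent model, but in the one-covariate case simulated here the rule is conservative, at about 3% to 4%.

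**Conclusion.** The point holds in limited form. The covariates for the main hypothesis tests depend on observed imbalance, and the 5-week t test omits the baseline adjustment that the 28 per arm requires. For 5-week systolic BP, always including baseline would raise power by about 17 to 18 percentage points: from 45.0% (t test) or 45.5% (rule, assumed 0.05 cut-off) to 62.6% at 28 per arm, and from 53.8% or 54.8% to 72.3% at 35.

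The harm is lost precision and a model not fixed in advance. The documents do not support attributing the power loss mainly to the imbalance rule, claiming excess false positives, or applying the 5% figure to the mixed model.

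The figures rest on the protocol's SD, correlation and effect, on normal data with equal SD at each visit and no missing values, and on the assumed cut-offs. No figure is given for chance selection of other covariates, because the article does not close the list.

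**What to change.** 1. Delete the sentence that lets baseline discrepancies inform the covariates, and delete the tests of randomisation success. Report the baseline table descriptively.
2. Replace the 5-week t tests with ANCOVA adjusted for the baseline value of the same BP measure, sex and antihypertensive use at randomisation, whatever imbalance is seen.
3. In the mixed model, add sex and antihypertensive use. Use baseline BP either as a response at week 0 or as a covariate with only the 5- and 12-week values as responses, but not both.
4. Label any further adjustment as a sensitivity analysis.

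ANCOVA at 5 weeks alone does not restore the planned 80%. That figure belongs to the baseline-adjusted mean of the two follow-ups, so the text should say which analysis the sample size supports.

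The cost is a change of wording before any unblinded analysis. The variables needed are already collected, and no participants are added.

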#### Aim 1: Determine the Efficacy of the ¡Alégrate! Web-Based Positive Psychological Intervention in Improving BP Control in Hispanic/Latino People With Hypertension From Baseline, Immediately Postintervention (5 Weeks), and at 12 Weeks After Baseline 

Independent samples *t* tests will be performed using 5-week systolic BP and diastolic BP as the dependent variables, with treatment condition serving as the grouping variable. Other model-based approaches to handle missing data, such as weighted estimating equations, will be implemented. We will also use mixed-effects models to compare changes in BP between the control and intervention arms as measured at baseline, 5 weeks, and 12 weeks. The independent variables include a time variable t (t=0, 5, 12), a dummy variable N (N=1, if PP intervention group; N=0, if attention control), and a cross-product term (t×N). For ambulatory data collected across a 24-hour period, sensitivity analyses will compare mean overall daytime versus nighttime values of BP. All data analyses were conducted using SAS 9.4 software (SAS Institute).

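### The 28 per arm was sized for baseline-adjusted ANCOVA over two follow-ups, but Aim 1 leads with an unadjusted 5-week t test that has about 45% power, not 80%

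*Protocol article*

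**What the plan says.** **Sample size (Planned Analyses).** The target is "differential and clinically meaningful improvements in systolic BP of 6 mm Hg compared with an attention control condition". Systolic BP is measured at baseline, 5 and 12 weeks. The inputs are a between-subject SD of 12 mm Hg, a within-subject correlation of 0.60, "a two-sided type I error probability of 0.05" and "80% statistical power". The article then argues that "adjusting for baseline measures (analysis of covariance) results in a more efficient analysis for a given sample size", and continues: "This approach yields an estimate of the required sample size of 28 participants per study arm under equal allocation". An allowance of 20% for attrition follows; the Abstract gives a total of 70.

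**Analysis (Aim 1).** The first analysis named is an independent-samples t test: "tests will be performed using 5-week systolic BP and diastolic BP as the dependent variables, with treatment condition serving as the grouping variable". A mixed-effects model is added after it, with linear time (0, 5, 12), a group indicator and their product as independent variables. Neither analysis is labelled primary.

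**Covariates (Planned Analyses).** Baseline variables enter the main models only if they are found to differ between arms. Adjustment for baseline BP is therefore not fixed in advance.

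**The concern.** The efficiency the article claims for ANCOVA comes from two sources: adjusting for baseline and averaging two follow-up readings. The 5-week t test gives up both, yet the sample size is the one that needs both. If the true effect is the 6 mm Hg the trial was designed to find, the first-named test would miss it more often than not. A null result could then be taken as lack of efficacy, although the same data analysed as the trial was sized would have had about 80% power. With two analyses listed and neither called primary, the choice between them could also be made after the results are known.

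**Working it through.** **Inputs**, all from Planned Analyses except the total of 70 (Abstract): difference δ = 6 mm Hg, SD σ = 12 mm Hg, ρ = 0.60, two-sided α = 0.05, power 80%, one baseline and two follow-ups, 28 per arm before attrition, attrition 20%.

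**Formula.** n per arm = 2(1.96 + 0.8416)² σ² f / δ² = 62.79 × f. Here f is the variance of the analysed quantity relative to a single reading. For r follow-ups and one baseline, with equal correlations:

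- follow-up only: f = (1 + (r−1)ρ)/r
- change from baseline: f = (1 + (r−1)ρ)/r + 1 − 2ρ
- ANCOVA: f = (1 + (r−1)ρ)/r − ρ²

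**Step 1: reproduce the 28.**

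| Follow-ups used | Analysis | f | n per arm |
|---|---|---|---|
| 1 | follow-up only | 1.00 | 62.8 → 63 |
| 1 | change | 0.80 | 50.2 → 51 |
| 1 | ANCOVA | 0.64 | 40.2 → 41 |
| 2 | follow-up mean | 0.80 | 50.2 → 51 |
| 2 | change | 0.60 | 37.7 → 38 |
| 2 | ANCOVA | 0.80 − 0.36 = 0.44 | 27.6 → **28** |

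Only the last row gives 28. Dividing by 0.80 for attrition gives 28/0.80 = 35 per arm, or 70 in total, which agrees with the Abstract. The article does not say in words that the two follow-ups are averaged, but its three-visit design and this arithmetic point to that variant.

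**Step 2: the t test on the 5-week value (f = 1.00).**

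- SE at 28 per arm = 12 × √(2/28) = 3.21 mm Hg. For the ANCOVA in the last row it is 12 × √0.44 × √(2/28) = 2.13 mm Hg.
- Power for 6 mm Hg at 28 per arm: 45.1% (noncentral t), 46.4% (normal approximation).
- Power if all 35 per arm are observed: 54.1% and 55.2%.
- Detectable difference at 80% power and 28 per arm: about 9.1 mm Hg (noncentral t). The normal approximation gives 2.8016 × 3.207 = 8.98.
- Completers needed for 80%: 63 per arm by the formula above, 64 by the exact t calculation. With 20% attrition, 63/0.80 rounds up to 79 per arm, or 158 in total.

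**Step 3: the ANCOVA variants at 28 per arm.** For week 5 alone (f = 0.64), power is 63% (noncentral t) or 65% (normal). For the mean of weeks 5 and 12 (f = 0.44), it is 79% or 80.5%, which matches the stated 80%.

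**Step 4: the mixed model's time-by-group term.** The article gives no covariance structure or time course for the effect, so this step assumes compound symmetry with ρ = 0.60 and two possible time courses.

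- The times 0, 5, 12 have mean 5.667, with sum of squared deviations 72.67.
- SE of the slope difference at 28 per arm = √(2 × 144 × 0.40 / (72.67 × 28)) = 0.238 mm Hg per week.
- Effect of 6 mm Hg at both follow-ups: fitted slope difference 0.468, ratio to SE 1.97, power about 50%.
- Effect growing linearly to 6 mm Hg at week 12: slope difference 0.5, ratio 2.10, power about 56%.

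With all 35 per arm observed, these become about 59% and 65%.

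**The case against.** The best counter-argument is that the t test is only listed first. The Aim 1 heading, the definition of the primary outcome as change over time, and the repeated-measures sizing all point at least as much towards the mixed model, and a statistical analysis plan that we have not seen may name it as primary. It is fair that lead status is inferred from order, and that 45% is the lowest of the figures for the two listed analyses, which run from about 45% to 65% depending on analysis, dropout and assumed time course. But all of that range lies below 80%. The mixed model treats baseline as an outcome rather than a covariate and tests a slope, so it does not supply the analysis the trial was sized on.

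A second objection is that averaging the two visits changes the question, since the first aim asks about 5 weeks and 12 weeks. That is a real trade-off: baseline-adjusted ANCOVA at week 5 alone reaches only about 63%, so the stated power is recovered only with the averaged effect as lead contrast. The averaged effect is, however, the one the calculation already assumed, and visit-specific effects can still be reported.

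Third, under randomisation the t test is unbiased with a valid type I error, and this is a phase II pilot. Both are true. The loss is one of precision, but the article states 80% power for a test of initial efficacy, and that statement should fit the test.

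The intervention content is released only after earlier content is completed (Content of the Intervention), so some participants may be mid-course at week 5. The article gives no figure for this, and nothing above depends on it.

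**Conclusion.** The concern holds. The 28 per arm and total of 70 are arithmetically sound for baseline-adjusted ANCOVA on the mean of the 5- and 12-week values, and that analysis is not in the plan. On the article's own inputs, the first-named Aim 1 test has about 45% power at 28 completers per arm and 54% with no dropout. Its standard error is 3.21 rather than 2.13 mm Hg, and its detectable difference is about 1.5 times the target (9.1/6). These figures need only the stated difference, SD and α; the correlation does not enter the t test. The 50 to 56% for the mixed model at 28 per arm also rests on our assumptions of compound symmetry and the two time courses. This should be corrected before the data are analysed.

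**What to change.** Replace the t test as the lead Aim 1 analysis. Model systolic BP at 5 and 12 weeks together, adjusted for baseline systolic BP in every case and not only when an imbalance is seen. Name the treatment effect averaged over the two visits as the lead contrast, and report the 5-week and 12-week effects after it. Power at 28 completers per arm is then 79 to 80%, as stated.

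If the 5-week t test is kept as lead, restate its power for 6 mm Hg as about 45% at 28 per arm, with a detectable difference of about 9 mm Hg. In either case, say which analysis is primary.

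The cost is a change of wording in Planned Analyses and Aim 1. Baseline BP is already measured before randomisation, and no further data or participants are needed.

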#### Aim 2: To Test Intervention Effects on Psychological Well-Being and Adherence to Healthy Behaviors and to Subsequently Explore Whether Improvements in Psychological Well-Being and Adherence to Healthy Behaviors Are Responsible for Better BP Control, That Is, Mediation Testing

Similar analytic techniques will be implemented for Aim 2 as used for Aim 1. The interaction of Group×Time will test if greater improvements are evident for psychological well-being and engagement in healthy behaviors (eg, dietary intake and self-reported physical activity) at 5 weeks postbaseline for the treatment arm as compared with the active control group. RM-ANOVA will also be used to examine whether the *¡Alégrate!* intervention is associated with greater improvements in psychological well-being and engagement in healthy behavior. In addition to reporting nominal *P* values, we will document the number of tests conducted and associated Bonferroni correction. Finally, we will conduct mediation analysis to test whether psychological well-being and healthy behaviors serve as intermediates (or mediators) through which *¡Alégrate!* impacts BP control. Tests of mediation will follow the recommendations of Shrout and Bolder to bootstrap product terms using Mplus. Given the dependency of indirect effects on the time interval, for multiwave models, we will compute overall, rather than time-specific, indirect effects.

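### The Aim 1 mixed model tests a straight-line slope difference, so its t×N term does not estimate the 5-week effect that Aim 2 assigns to Group×Time

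*Protocol article*

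**What the plan says.** Planned Analyses sets Aim 1 as efficacy in "reducing B*P* values immediately postintervention (ie, 5 weeks) and at the 12-week follow-up period, that is, Exams 2 and 3". The Aim 1 section then names two comparisons of the arms.

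- First: "Independent samples *t* tests will be performed using 5-week systolic BP and diastolic BP as the dependent variables", grouped by arm.
- Second: "We will also use mixed-effects models to compare changes in BP between the control and intervention arms as measured at baseline, 5 weeks, and 12" (the last figure is also in weeks). For this model, "The independent variables include a time variable t (t=0, 5, 12), a dummy variable N" for arm, "and a cross-product term (t×N").

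The same section mentions weighted estimating equations for missing data, without giving a form for time.

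Aim 2 uses similar techniques. It states that "The interaction of Group×Time will test if greater improvements are evident for psychological well-being and engagement in healthy behaviors", and it places that comparison "at 5 weeks postbaseline for the treatment arm as compared with the active control group". Repeated-measures ANOVA is also named there. The sample-size paragraph in Planned Analyses rests on an analysis adjusted for baseline, not on a slope.

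**The concern.** Only the arm variable is called a dummy. Time is a single variable taking the values 0, 5 and 12, with one product term; three categorical visits would need two. The model therefore assumes that the arm difference grows by the same amount each week up to week 12. The course lasts 5 weeks, so an effect that levels off or weakens after week 5 is plausible, and the article gives no reason to expect steady growth.

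Two things are at stake. A slope over 12 weeks is not the 5-week contrast that Aim 2 says it is. For BP, the model gives no separate week-5 and week-12 effects, although Aim 1 asks about both visits.

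**Working it through.** **Inputs.** From the sample-size paragraph in Planned Analyses: difference 6 mm Hg, SD 12, within-subject correlation 0.60, two-sided 0.05, 80% power, 28 per arm, 20% attrition. From Aim 1: t = 0, 5, 12. Assumed here: compound symmetry, complete data, normal approximation, and the effect profiles below, which are illustrative. Benefits are written as positive numbers.

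**The plan's own figure.** With one baseline and two follow-up measures, the baseline-adjusted variance factor is (1 + 0.60)/2 − 0.60² = 0.44. Then n = 2 × 144 × 0.44 × (1.96 + 0.842)²/36 = 27.6, so 28 per arm; 28/0.80 = 35 per arm, 70 in total. The figure reproduces, and it belongs to the baseline-adjusted mean of the two follow-up visits.

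**What t×N estimates.** Mean t = 17/3 = 5.667. Deviations are −5.667, −0.667 and 6.333, with sum of squares 72.67. Dividing the deviations by 72.67 gives weights of −0.0780 (week 0), −0.0092 (week 5) and +0.0872 (week 12). Week 5 carries about a tenth of the week-12 weight, with the opposite sign.

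**Standard errors at 28 per arm.**
- Slope difference: √(2 × 144 × 0.4/(28 × 72.67)) = 0.238 mm Hg per week.
- Unadjusted 5-week t test: 12 × √(2/28) = 3.21. For 6 mm Hg, z = 1.87 and power is about 47%.
- Baseline-adjusted contrast at one visit: 12 × √(0.64 × 2/28) = 2.57.
- Baseline-adjusted mean of both visits: 12 × √(0.44 × 2/28) = 2.13.
- Unadjusted change from baseline to week 12: 12 × √(0.8 × 2/28) = 2.87.

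**Expected slope and power.** Slope = −0.0092 × (week-5 effect) + 0.0872 × (week-12 effect).

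| Effect at weeks 5, 12 | Slope per week | t×N | Change to week 12 | Categorical 2-df | Adjusted week 5 | Adjusted mean |
|---|---|---|---|---|---|---|
| 6, 6 | 0.468 | 50% | 55% | 57% | 65% | 80% |
| 6, 3 | 0.206 | 14% | 18% | 45% | 65% | 56% |
| 6, 0 | −0.055 | 6% | 5% | 57% | 65% | 29% |
| 2.5, 6 (linear) | 0.500 | 56% | 55% | 45% | 16% | 52% |

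**Size of the week-5 error.** With 6 mm Hg at both visits, the slope implies 5 × 0.468 = 2.3 mm Hg of change by week 5. The model also fits a baseline gap of 1.35 that does not exist. Even with that added, the fitted week-5 difference is 3.7, not 6.

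**When the sign changes.** The slope reverses when the week-12 effect is below 0.667/6.333 = 10.5% of the week-5 effect.

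**Sensitivity.** If all 35 per arm are followed, t×N power is 59% for the 6, 6 profile and 16% for 6, 3. If the correlation instead decays from visit to visit (0.60 between adjacent visits, 0.36 between the first and last), the 6, 6 profile gives t×N 31% against 47% for the 2-df test, and the sign threshold rises to 20%.

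**The case against.** The strongest reply is that the plan does not rely on t×N for BP at week 5. The t tests come first and estimate the 5-week difference without bias whatever happens later. For week 12 the slope is a fair proxy: 12 × slope is 5.6, 2.5 and −0.7 mm Hg when the true week-12 effects are 6, 3 and 0, and its standard error (12 × 0.238 = 2.86) nearly equals that of the direct change contrast (2.87). This stands. A reader might infer that the plan cannot test the 5-week BP effect at all; the Aim 1 section does not support that.

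Three other inferences also go too far.

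- **That linear coding explains the whole drop from 80% to 50%.** With a sustained effect it costs 5 to 7 points (55% or 57% against 50%). The rest comes from not adjusting for baseline and not averaging the visits. In the 6-to-3 fade, a direct unadjusted week-12 contrast would itself have only 18%.
- **That the slope is likely to point the wrong way.** This needs a near-complete fade, which the article does not predict. It describes skills being built into daily life.
- **That Aim 3 inherits the problem.** Table 2 collects blood spots at baseline and once after the intervention. Although the recruitment text lists blood spots among the visit procedures generally, Table 2 sets the schedule. With two time points, linear and categorical time are the same model.

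For Aim 2, repeated-measures ANOVA usually treats time as a factor, and a model using only baseline and week 5 would isolate the 5-week change. The text specifies neither for the Group×Time test and refers back to the Aim 1 techniques. It is also fair that an article condenses and never uses the word linear. But the coding and the single product term are stated here, not left to another document.

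**Conclusion.** The point holds for the t×N term, not for the whole plan. As written, the term is a slope difference driven by week 12 versus baseline. It does not estimate the 5-week effect that Aim 2 assigns to it, and it does not give separate week-5 and week-12 BP effects. The week-5 BP question is left to unadjusted t tests with about 47% power for 6 mm Hg, and the week-12 question has no named contrast of its own.

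The power loss depends on the shape of the effect: modest against a categorical test if the effect is sustained (50% against 57%), large if it halves (14% against 45%). Both Aim 1 tests fall well short of the 80% that justified the sample size, partly because neither is stated to adjust for baseline. These figures rest on compound symmetry, complete data and assumed profiles. They apply to systolic BP; for the Aim 2 outcomes the weights carry over, but the article gives no SD from which to compute power.

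**What to change.** For Aims 1 and 2, replace numeric t with visit as a categorical factor. Either adjust for the baseline value, or keep baseline in the outcome vector with its mean constrained equal across arms. Prespecify the arm contrasts at week 5, at week 12 and their average, and state which of them Group×Time refers to in Aim 2. The average contrast is the one that matches the sample-size calculation. Aim 3 needs no change on this account.

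The cost is a sentence of specification and one extra parameter, with no new data. There is a real trade-off: if the effect truly grew in a straight line to week 12, the 2-df test would have 45% power against 56% for the slope. Settle the change before outcomes are compared by arm, so that it is not a post hoc choice of model.
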